**Methods and analysis:**

This world-first double-blind trial will aim to randomise 100 participants with PTSD+AUD to a regimen of Concurrent Treatment of PTSD and Substance Use Disorders Using Prolonged Exposure (COPE) (12 sessions)+MDMA (80–160 mg: 2 dosing and 2 integration sessions) or COPE (12 sessions)+active control (niacin 250 mg: 2 dosing sessions and 2 integration sessions). All participants will receive medical management. The primary PTSD outcome will be the clinician-administered PTSD Scale for DSM-5. The primary drinking outcome will be the number of heavy drinking days (HDDs) per week, validated by phosphatidylethanol. Secondary PTSD and alcohol-related outcomes will include PTSD checklist for DSM-5 scores, absence of any HDDs and standard drinks per drinking day. We will also examine change in other clinical conditions and symptoms including depression, sleep disturbances and post-traumatic cognitions; treatment satisfaction and engagement; adverse events; and cost-effectiveness.

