**Trial registration number:**

NCT05709353.

STRENGTH AND LIMITATIONS OF THIS STUDYA strength of the MDMA-assisted PTSD and Alcohol Therapy Trial (MPATHY) trial is that it targets a common and challenging comorbidity (post-traumatic stress disorder (PTSD) with comorbid alcohol use disorder) that is not addressed in the majority of other 3,4-methylenedioxymethamphetamine (MDMA)-assisted therapy trials for PTSD.The MPATHY trial will minimise bias due to the use of the gold standard objective biomarker phosphatidylethanol to validate alcohol consumption data.The MPATHY trial will minimise bias due to the randomised and double-blind design in addition to the inclusion of an active control and prospective stratification for expectancy.The MPATHY trial is that it leverages an evidence-based behavioural intervention with strong empirical support for all participants.A potential limitation of this trial is the comprehensive nature of the evidence-based intervention combined with MDMA which may be resource intensive.

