#### Medical/laboratory tests

These tests screen participants for exclusion criteria, assess potential AEs, provide objective measures of alcohol use and assess covariates and secondary outcome measures. The physical examination at screening includes BP, HR, ECG, height, weight, full blood count, LFTs (bilirubin, Gamma-Glutamyl Transferase, Alkaline Phosphatase, Aspartate Aminotransferase, Alanine Aminotransferase, albumin, protein), coagulation (International Normalised Ratio, Activated Partial Thromboplastin Time), urine toxicology, concomitant medications, withdrawal symptoms (CIWA-Ar). All abnormal findings will be reviewed by the physician, and participation is endorsed or further evaluation performed as clinically indicated. Tests will be repeated if clinically indicated and for baseline measurement if required. PEth is collected at screening/baseline, mid-point (visit 8) and end of treatment (visit 18). Blood samples will also be collected and stored for biochemical and genetic exploratory analyses relating to the current trial and for future use in ancillary studies.

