##### Secondary

The secondary outcome will be alcohol consumption expressed as self-reported number of heavy drinking days (HDDs) per week, defined as >4 drinks for women, ≥5 drinks for men (where a single standard drink is defined by 10 g of ethanol). Any conflicting information will be validated by collateral reports (provided by electronic medical records or clinicians) and measurement of biological markers of alcohol consumption (PEth). We will also examine absence of any HDDs per week over treatment period and standard drinks per drinking day (DDD).

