It has been suggested that the effect sizes in MDMA trials have been overestimated in previous studies due to poor methodology^34^ including: (1) strong expectancy effects; (2) sample sizes are small leading to wide variation in estimates; (3) objective outcome measures are rarely used; (4) failure to maintain blinding of participants (with few studies assessing and reporting on blinding); (5) poor control with regards to which specific therapeutic elements are used throughout therapy and which different elements are impactful and (6) no inclusion of gold-standard evidence-based therapeutic comparators. Accordingly, we will conduct a double-blind RCT that includes an active control, prospective stratification for expectancy, objective alcohol outcome measures, comprehensive evaluation of AEs, independence from commercial interest and partnership with advocacy groups and, importantly, utilisation of specific evidence-based therapeutic modalities for comorbid PTSD and AUD as the ‘base’ therapy.

Improving the therapeutic benefit of integrated exposure therapy for PTSD+AUD remains a challenge particularly given the presence of comorbidities that may be contraindicated for certain medications such as MDMA. The MPATHY trial thus has the potential to facilitate the development of alternate options to optimise integrated exposure therapy but also to add to the literature regarding the suitability of MDMA-assisted therapy for this comorbid population in light of existing, safe, evidence-based gold-standard therapies.

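### PEth is presented as giving objective alcohol outcomes, but every alcohol outcome the plan names rests on reported drinking and the outcomes section uses PEth only to check conflicts

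*Protocol article*

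**What the plan says.** The protocol article describes PEth in five places.

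- **Outcomes, Secondary.** The alcohol outcome is defined thus: "The secondary outcome will be alcohol consumption expressed as self-reported number of heavy drinking days (HDDs) per week". The section adds: "We will also examine absence of any HDDs per week over treatment period and standard drinks per drinking day (DDD". PEth appears once, as "measurement of biological markers of alcohol consumption (PEth"; the full sentence makes conflict the trigger: "Any conflicting information will be validated by collateral reports (provided by electronic medical records or clinicians) and measurement of biological markers of alcohol consumption (PEth".
- **Abstract, Methods and analysis.** "The primary drinking outcome will be the number of heavy drinking days (HDDs) per week, validated by phosphatidylethanol". No conflict is needed to trigger this.
- **Strengths and limitations box.** The trial is said to minimise bias through the "use of the gold standard objective biomarker phosphatidylethanol to validate alcohol consumption data". Again there is no trigger.
- **Medical/laboratory tests.** The tests as a group are said to "provide objective measures of alcohol use and assess covariates and secondary outcome measures". PEth is among them and is drawn on a fixed schedule.
- **Discussion.** After noting that earlier MDMA trials rarely used objective outcomes, the article offers "prospective stratification for expectancy, objective alcohol outcome measures" as part of its answer.

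The Statistical analysis section names models for CAPS-5 and for heavy drinking days per week. It then covers other outcomes collectively, with adjustment for multiple comparisons, and does not mention PEth. The Medications section plans to record allocation guesses by participant, clinician and researcher, and a sensitivity analysis by guessed allocation.

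**The concern.** The Discussion claims a design feature that the outcomes list does not contain. This matters because the plan itself treats expectancy and failed blinding as live risks: it stratifies on expectancy and records guesses. If participants who believe they received MDMA report less drinking than they consumed, that error enters every named alcohol outcome. Reduced alcohol consumption is the second hypothesis, and alcohol use disorder is half of the comorbidity under study. A reader who relies on the claim would give the alcohol result more protection from reporting bias than the stated outcomes provide.

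**Working it through.** **1. Source of each named alcohol outcome.** Heavy drinking days per week is self-reported by definition. Absence of heavy drinking days derives from the same reports. Drinks per drinking day is a drink count, and Questionnaires and tasks collects drinking by Timeline Follow-Back. So none of the three is a biomarker outcome.

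**2. The plan's own figure.** No sample size or power figure is given for alcohol or PEth. The only one is N = 100 for CAPS-5. It reproduces closely with a between-arm repeated-measures F test, noncentrality λ = N·f²·m / (1 + (m − 1)ρ), f = 0.25, ρ = 0.5, 80% power. Assuming m = 3 measures (the number is not stated), 86 analysable participants are needed, and 86 / 0.85 = 101.2, so 102 when rounded up to equal arms. That figure is not in dispute. It supplies the analysable number used below: 50 × 0.85 = 42.5 per arm.

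**3. What a conflict-triggered check can see.** If reports in one arm are shifted on average by δ relative to the other, then

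expected observed difference = true difference + δ.

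A check set off by contradictions acts on individual records. A modest shift spread over an arm need not make any one record contradictory, yet δ passes in full into the arm comparison. Collateral from clinicians is not fully independent of this, since clinicians are among those whose guesses are recorded.

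**4. Illustration of size.** The documents give no δ, so it is assumed. With no true effect, unit SD and a two-sample normal approximation:

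- standard error = √(2 / 42.5) = 0.217 SD
- z-shift = δ / 0.217
- rejection probability = 1 − Φ(1.96 − z-shift) + Φ(−1.96 − z-shift)

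| Assumed δ (SD) | z-shift | Two-sided rejection at nominal 5% |
|---|---|---|
| 0.10 | 0.46 | 7.5% |
| 0.15 | 0.69 | about 11% |
| 0.20 | 0.92 | 15% |
| 0.25 | 1.15 | about 21% |
| 0.30 | 1.38 | 28% |

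The planned analysis is a mixed count model over repeated measures, so these values show scale only.

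**5. What a PEth comparison could detect.** For a baseline-adjusted comparison at one time point, the difference detectable with 80% power is √(1 − r²) × (1.96 + 0.84) × 0.217 SD. For an assumed baseline correlation r of 0.3, 0.5 or 0.7 this gives 0.58, 0.53 or 0.43 SD. Power at 0.5 SD is 68%, 76% or 90%. The comparison is informative, but a null result would not by itself refute a heavy-drinking-day effect.

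**6. Timing.** Procedures and schedule of visits draws PEth at visits 8 and 16, makes visit 16 the end of treatment and visit 18 the last follow-up. Medical/laboratory tests puts the end-of-treatment PEth sample at visit 18. These cannot both hold.

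**The case against.** Several objections have force.

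- A reader might infer that PEth is used only to settle conflicting self-reports. The documents do not support that. The abstract and the strengths box describe general validation, the laboratory section links its tests to objective alcohol measures and secondary outcomes, and samples are scheduled rather than triggered.
- A reader might infer that PEth will not be compared between arms. That is silence, not a statement. The collective sentence on other outcomes could cover it, and the model, scale and time points are details an article may leave to the full protocol or analysis plan.
- A reader might call PEth the only objective alcohol measure. Liver function tests, including gamma-glutamyl transferase, and breath alcohol at dosing are also taken, and record-based collateral is another check beyond self-report. They serve mainly clinical or checking purposes, but the absolute wording fails.
- The sensitivity analysis by guessed allocation addresses the same mechanism. It is a real mitigation, but a participant who improves may guess MDMA because of the improvement, so it cannot separate drug effect from biased reporting.
- The false-positive figures rest on an assumed shift and would apply to any self-reported outcome.

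What remains is a conflict between stated passages: the article lists its alcohol outcomes, none is objective, and it claims objective alcohol outcomes as a strength.

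**Conclusion.** The point holds as an inconsistency with a practical consequence. PEth's role is wider in the abstract, strengths box, laboratory section and Discussion than in the outcomes section, and no named alcohol outcome is free of reporting bias. Neither the conflict-triggered check nor the analysis by guessed allocation would remove a systematic between-arm shift in self-report. How large such a shift would be is unknown; the range of about 11% to 21% depends wholly on the assumed 0.15 to 0.25 SD and is not an estimate. The consequence is confined to the alcohol conclusions, which the outcomes section ranks as secondary. The primary CAPS-5 conclusion and the sample size are unaffected. The change should be made, but the trial's main result does not depend on it.

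**What to change.** 1. Reconcile the end-of-treatment PEth visit (16 or 18) across the visit schedule and the laboratory section.
2. State PEth's role once and use the same description throughout.
3. Name baseline-adjusted change in PEth, for example on the log scale, as a secondary alcohol outcome compared between randomised arms at mid-point and end of treatment. Report it beside the heavy-drinking-day result, and keep the check on conflicting information as an addition.
4. If this is not wanted, withdraw the claim of objective alcohol outcome measures.

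The cost is one entry in the outcomes list, one more model and one more outcome in the multiplicity adjustment. Samples are already scheduled and N does not change. Study assessments allows follow-up data by telephone, so participants reached only that way will have no PEth value; the number missing by arm should be reported and the comparison read with that in mind.

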##### Additional clinical outcomes

We will also examine change in other clinical conditions and symptoms listed above including depression (DASS), sleep disturbance (ISI), health-related quality of life (SF-36) PTCI.

##### Safety outcomes

Safety will be analysed using categorical outcomes, defined by the type and severity of AEs assessed throughout the trial (in addition to ongoing measures of suicidality and mood as listed above). AEs will also be systematically recorded as per the COMBINE SAFTEE tool in the week following each dosing.

##### Feasibility outcomes

Engagement will be examined via the treatment satisfaction assessments (YES, CSQ) plus treatment retention and adherence. Uptake will be examined via recruitment rate (participants/month/site), screening-to-enrolment ratio and the reasons for exclusion/refusal.

### Sample size calculations

This study is sufficiently powered to estimate the effects of COPE+MDMA versus COPE+Control on significant reductions in clinician-administered PTSD symptom severity over time (CAPS-5). For the COPE+Control, based on our previous COPE trial^17^ we assume a 26% reduction in CAPS-5 score from baseline to treatment completion (Week 14) and a 42% reduction from baseline to longer follow-up. For COPE+MDMA, based on prior work of MDMA-assisted therapy,^71 72^ we assume a 55%–63% reduction from baseline. We consider these estimated separations of CAPS-5 data over repeated measures. To achieve >80% power for a two-sided test at α=0.05 conservatively assuming a within-participant correlation of 0.5 and 15% data loss, based on prior studies,^47^ 50 participants will be needed per arm (active vs control) (n=100) for the effect of MDMA versus control, time and treatment×time where the groups separate to a medium to large effect (f=0.25, Cohen’s d=0.5–0.7).

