#### Outcomes

##### Primary

The primary outcome is PTSD symptom severity as assessed by the CAPS-5 from baseline to end of treatment (visit 16). CAPS-5 is a structured diagnostic interview with excellent psychometric properties and diagnostic efficiency and used widely in MDMA-assisted PTSD studies. The CAPS-5 will be administered by independent evaluators blind to treatment condition. We will also examine secondary PTSD outcomes including change in self-reported PTSD symptom severity via the PCL-5 from baseline to visit 16. PCL-5 has excellent psychometric characteristics for a secondary indicator of PTSD symptom severity.

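### The claimed >80% power does not hold for the visit-16 primary contrast or for treatment×time at d=0.5, the low end of the plan's own effect range

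*Protocol article*

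**What the plan says.** All references are to the protocol article.

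- **Sample size calculations.** The design target is set out as "To achieve >80% power for a two-sided test at α=0.05 conservatively assuming a within-participant correlation of 0.5 and 15% data loss". From this the section arrives at 50 per arm, 100 in total, and applies that figure to three effects at once: arm, time and their interaction. The effect size is put in these terms: "where the groups separate to a medium to large effect (f=0.25, Cohen’s d=0.5–0.7"). The section says that the separations are considered over repeated measures but does not give the number of occasions. It assumes a 26% CAPS-5 reduction on control at treatment completion and 42% at longer follow-up, against 55–63% on MDMA. No SD is given.
- **Outcomes, Primary.** "The primary outcome is PTSD symptom severity as assessed by the CAPS-5 from baseline to end of treatment (visit 16").
- **Statistical analysis.** CAPS-5 is compared between arms over repeated measures with a mixed effects model.
- **Discussion.** The article reports the suggestion that "effect sizes in MDMA trials have been overestimated in previous studies due to poor methodology".

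**The concern.** The power statement covers three different effects with one f value, while the primary outcome is tied to a single post-baseline time point. Three things do not fit together.

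1. A repeated-measures group effect averages over all occasions, so its power is not the power of the visit-16 contrast.
2. For two arms f is half of d, so one f cannot stand for a range of d. The same f also means something different when it is entered for an interaction.
3. The assumed percentage reductions are never converted to d.

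At stake is how the result is read. The article calls the trial sufficiently powered (Sample size calculations) and well-powered (Discussion). If the true effect is near d=0.5, a non-significant visit-16 result would be less informative than those words suggest. The MDMA-arm assumption comes from prior MDMA-assisted therapy work, and the Discussion itself reports doubts about the size of such effects, so the low end of the range deserves a correct figure.

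**Working it through.** **Inputs** (Sample size calculations): two-sided α=0.05; N=100, 50 per arm; 15% loss, so 100 × 0.85 = 85 evaluable, 42.5 per arm; ρ=0.5; f=0.25, d=0.5–0.7. The number of occasions m is not stated, so I take 2, 3 and 4. Powers use the noncentral F or t distribution.

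**1. Effect-size conversion.** For two equal arms f = d/2. So f=0.25 is d=0.5, and d=0.7 is f=0.35.

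**2. Reproducing N=100.** Repeated-measures ANOVA, between-group effect: λ = N·f²·m / (1 + (m−1)ρ), with 1 and N−2 df.

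| m | λ at N=85 | Power at N=85 | N for 80% | N after 15% loss |
|---|---|---|---|---|
| 2 | 7.08 | 74.9% | 98 | 116 |
| 3 | 7.97 | 79.7% | 86 | 102 |
| 4 | 8.50 | 82.2% | 82 | 97 |

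The plan's 100 lies between the figures for three and four occasions. This calculation takes the arms to differ by d=0.5 at every occasion. If baseline is one of the occasions, that includes baseline, where randomisation makes the expected difference zero. With four occasions, zero difference at baseline and d=0.5 at the other three, the mean difference is 0.375 and the power of the group main effect is 58%.

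**3. The visit-16 contrast.** Noncentrality = (d/s)·√(42.5/2), with s² = 2(1−ρ) = 1.0 for change from baseline and s² = 1−ρ² = 0.75 for the baseline-adjusted comparison. At d=0.5:

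- change: 0.5 × √21.25 = 2.30
- adjusted: (0.5/0.866) × √21.25 = 2.66

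| d | Change | Baseline-adjusted |
|---|---|---|
| 0.50 | 62.5% | 74.9% |
| 0.55 | 70.7% | 82.5% |
| 0.60 | 78.0% | 88.4% |
| 0.70 | 89.1% | 95.7% |

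80% is reached at about d=0.61 (change) and just above d=0.53 (adjusted); d=0.54 gives 81% adjusted.

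**4. Treatment×time.** With zero difference at baseline and d=0.5 at each later occasion, λ = N·Σ(δ−δ̄)²/4 / (1−ρ), where δ is the arm difference at each occasion and δ̄ its mean, with m−1 and (N−2)(m−1) df.

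| m | λ | Power |
|---|---|---|
| 2 | 5.31 | 62.5% |
| 3 | 7.08 | 65.3% |
| 4 | 7.97 | 64.5% |

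Entering f=0.25 directly as the interaction effect gives more than 99% power. With two occasions the interaction f is d/4, so f=0.25 there means d=1.0, which is outside the stated range.

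**5. Average over follow-ups, baseline-adjusted.** For k follow-ups s² = (1+(k−1)ρ)/k − ρ². At d=0.5, k=2 gives s²=0.50 and 89.6% power; k=3 gives s²=0.417 and 94.2%.

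**6. Assumed reductions.** At treatment completion the arms separate by 55−26 = 29 to 63−26 = 37 points of the baseline mean. For d=0.5 the SD would have to be 29/0.5 = 58% to 37/0.5 = 74% of the baseline mean; for d=0.7, 29/0.7 = 41% to 37/0.7 = 53%. If instead the SD were 20–40% of the baseline mean (my assumption), d would be 29/40 = 0.72 to 37/20 = 1.85 and visit-16 power at least about 91%, even as a change score.

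**The case against.** The strongest defence is that the article never states >80% for a visit-16-only contrast. It states power over repeated measures and plans a mixed model over repeated measures, and on that basis N=100 comes out within about 3%. A reader might infer that the sponsor made a calculation error; the documents do not support that. Nor does power above 80% depend on an arm difference at baseline: a baseline-adjusted average of two or three follow-ups gives about 90–94% at d=0.5. That route needs CAPS-5 at the later visits. The 42% long-term assumption suggests such assessments, but the schedule is in a supplement that is not shown.

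This defence stands as far as it goes. It leaves two things unanswered. An average over follow-ups is not the endpoint that the Primary section fixes at visit 16. And treatment×time, which the power statement does name, does not reach 80% at d=0.5 with equal arms at baseline.

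A second objection is that the gap is small and sits at one end. Under the more efficient adjusted analysis it is about 5 points at d=0.5 and gone by d=0.54. The assumed reductions may also imply a larger d. Both points are right. They rule out the stronger inference that the trial is underpowered under its own assumptions.

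**Conclusion.** The point holds as a mismatch between the power statement and the primary endpoint, limited to the low end of the stated effect range. With 85 evaluable, ρ=0.5 and d=0.5, power is about 62% (change) or 75% (baseline-adjusted) for the visit-16 contrast, and about 62–65% for treatment×time over two to four occasions, against the >80% claimed. From about d=0.54 the baseline-adjusted visit-16 contrast exceeds 80%. The pairing of f=0.25 with d=0.5–0.7 is wrong at every value except d=0.5, and the link from the assumed reductions to d is missing.

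These results rest on equal arms at baseline, equal variances, a constant correlation of 0.5 across occasions and loss taken as 15% of participants. Which d is realistic cannot be settled from the article, because no SD is given. That the low end is the likely one is a judgement that the Discussion's remark prompts but does not establish.

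**What to change.** Keep N=100 and rewrite the power statement for the primary test:

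- Name the contrast: the baseline-adjusted difference in CAPS-5 at visit 16 from the mixed model, with 85 evaluable and correlation 0.5. State 75% power at d=0.5, 80% from about d=0.54 and 96% at d=0.7.
- Drop the blanket power claim for time and treatment×time.
- Correct the effect size: f=0.25 is d=0.5, and d=0.7 is f=0.35.
- State the SD that connects the 26% versus 55–63% reductions to d.

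The cost is a change of wording and slightly less favourable stated power at the low end. No extra participants are needed and the repeated-measures model stays.
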